To quantify the proportion of women who demonstrate levator ani muscle (LAM) co-activation—defined as an anteroposterior diameter change (APD) < 0 mm—at two time-points: (i) during the TPUS-guided training session, and (ii) at birth, where an intrapartum sonographic assessment is feasible within routine clinical care.To compare postpartum maternal satisfaction between the control and TPUS-guided intervention arms, as measured by the Childbirth Experience Questionnaire 2 (score range 0–100).To quantify the difference of prevalence in 1st-, 2nd-, 3rd- and 4th-degree perineal tears between the control and the TPUS-guided intervention arms.To measure the difference in total postpartum blood loss (mL) within 24 hours of delivery between the control and the TPUS-guided intervention arms.To compare the rates of spontaneous vaginal birth, operative vaginal birth and unplanned caesarean sections between the control and the TPUS-guided intervention arms.To evaluate the prevalence of stress or urge urinary incontinence at 6, 12, 16 weeks postpartum between the control and the TPUS-guided intervention arms, defined as an International Consultation on Incontinence Questionnaire-Urinary Incontinence Short Form (ICIQ-SF) score ≥ 6.To compare the proportion of women that require pharmacological augmentation during the active second-stage of labour between the control and TPUS-guided intervention arms.To quantify the association between persistent fetal malposition (non-occiput-anterior at full cervical dilatation and/or at delivery) and the length of the second stage of labour (minutes), and to test whether this association differs between the control and TPUS-guided intervention arms. This association is observational in nature and is not interpreted as a randomised comparison.

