### Data collections

Data will be collected at multiple time points throughout the study to ensure comprehensive evaluation of the interventions’ effectiveness and safety (Fig 1). At enrolment, baseline demographic and obstetric information, including maternal age, parity, medical history, and pregnancy details, will be recorded. During the intervention period, attendance and engagement with both the online educational video and in-person sessions will be tracked. For participants in the TPUS-guided arm, detailed observations and measurements captured through TPUS will be documented during practical exercises to assess technique and muscle engagement.

Delivery outcomes will be extracted from medical records, including mode of birth (vaginal or caesarean section), duration of second stage of labour, incidence of any degree perineal tears, and any complications. Following childbirth, women’s satisfaction with the delivery experience will be evaluated using validated questionnaires. Women will be contacted at 6, 12 and 16 weeks post-partum. At each time point, urinary incontinence will be assessed using the ICIQ-SF questionnaire. At the 16 weeks follow-up, women will additionally be asked whether they have attended pelvic floor rehabilitation sessions since delivery. Collected data will be handled using a secure, de-identified database, with regular checks to ensure data integrity and adherence to ethical guidelines. Pseudonymized datasets will be stored on Zenodo (https://zenodo.org/), a secure open-access platform compliant with EU data protection regulations and FAIR principles.

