The primary endpoint will be analysed using multivariable linear regression, with treatment arm as the main predictor. The model will be adjusted for pre-specified baseline covariates only, that is, variables measured before randomisation: maternal age, body mass index at enrolment, gestational age at randomisation, maternal height, and sonographic estimated fetal weight at the last available third-trimester scan. Consistent with ICH E9, no post-randomisation variable is included in the confirmatory model, since conditioning on variables measured after allocation may invalidate the randomisation-based causal interpretation of the treatment effect. This applies in particular to fetal head position at full cervical dilatation, epidural analgesia and gestational age at delivery, which are potential intermediate variables on the causal pathway between the intervention and the primary endpoint. Their distribution across arms will be reported descriptively, and epidural analgesia and fetal head position will be examined as potential effect modifiers through interaction terms, as exploratory analyses. The primary result will be reported as an adjusted mean difference with 95% confidence interval; the p-value will be provided as secondary inferential information. If the residuals of the linear model indicate substantial departure from normality, a bootstrap confidence interval will be computed. Women who do not reach the active second stage (e.g., caesarean delivery before full dilatation) will not contribute to the primary analysis but will be retained in the ITT population for all secondary outcomes. For clarity, the primary estimand may therefore be summarised as the difference in adjusted mean duration of the active pushing phase between arms among randomised nulliparous women reaching the active second stage, with operative vaginal delivery and second-stage caesarean section handled under a treatment-policy strategy as delivery events at the observed time. The number of women contributing to each analysis, with the corresponding denominators and reasons for non-contribution, will be reported by arm in the CONSORT flow diagram, and the baseline characteristics of women not reaching the active second stage will be compared between arms using standardised mean differences. Sensitivity analyses will include multiple imputation under the missing-at-random assumption and inverse probability weighting to assess the robustness of the primary estimate to differential attrition, applied to observations that are missing rather than undefined, such as incomplete partogram times or non-returned questionnaires; where an imbalance is observed in the proportion of women reaching the active second stage, inverse probability of selection weights will be applied accordingly. Time to spontaneous vaginal birth from the onset of active pushing will additionally be described using cumulative incidence functions, with operative vaginal delivery and second-stage caesarean section treated as competing events rather than as censored observations, and compared between arms using Gray's test. This analysis is supportive and exploratory.

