
Mode of delivery (spontaneous vaginal birth vs. operative vaginal or caesarean), perineal tears (≥ 3rd degree vs. none/1st–2nd degree), postpartum haemorrhage (≥ 500 mL vs. < 500 mL), and need for pharmacological augmentation during the active second stage will be analysed using logistic regression with the same set of pre-specified baseline covariates. Results will be reported as adjusted odds ratios with 95% CIs, accompanied by absolute risks and risk differences by arm to facilitate clinical interpretation. For endpoints with a low expected number of events, Firth's penalised-likelihood estimation will be used. Third- and fourth-degree perineal tears will be analysed among all women reaching the second stage, with caesarean deliveries counted as no injury, and additionally among women delivering vaginally. Mode of delivery is also addressed within the competing-risks analysis described above. Total postpartum blood loss (mL) and maternal satisfaction (CEQ-2 score) will be analysed using multivariable linear regression as described for the primary endpoint, reporting adjusted mean differences with 95% CIs, with bootstrap confidence intervals reported for blood loss in view of its expected skewness. Urinary incontinence (ICIQ-SF score ≥ 6) will be assessed at 6 weeks, 12 weeks and16 weeks postpartum. The outcome will be modelled using mixed-effects logistic regression with a random intercept for participant and fixed effects for treatment arm, time point, and their interaction, adjusted for the same baseline covariates. This approach accounts for within-subject correlation across repeated assessments and allows estimation of the treatment effect trajectory over time and makes use of all available observations under a missing-at-random assumption. Both the interaction term and the adjusted treatment effect at each time point will be reported. Attendance at postpartum pelvic floor rehabilitation, a post-randomisation variable, will be summarised descriptively by arm and, where uptake exceeds 10% in either arm, included in sensitivity analyses for pelvic floor–related outcomes as described above. Pre-specified subgroup analyses will examine potential effect modification by: (i) Within-arm analysis of levator ani function (intervention arm only); (ii) gestational age at intervention (28–34 weeks vs. 35–37 weeks); and (iii) epidural analgesia (yes/no). Subgroup (ii) and subgorup (iii) are defined by post-randomisation variables and are reported as exploratory only. Subgroup effects will be estimated via interaction terms in the regression models and reported as stratum-specific effect estimates with 95% CIs. All secondary, subgroup, and repeated-measures analyses are regarded as exploratory and hypothesis-generating. The trial is powered exclusively on the primary endpoint. Results of secondary analyses will be reported as point estimates with 95% confidence intervals without correction for multiplicity and should be interpreted in the context of the overall pattern of findings rather than as confirmatory evidence. All analyses will be conducted using R (R Foundation for Statistical Computing) and STATA (StataCorp LLC).

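### The tear objective names all four degrees, but the only stated analysis contrasts 3rd/4th degree with everything else, so 1st- and 2nd-degree tears get no between-arm estimate

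*Protocol article*

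**What the plan says.** Among the secondary objectives (protocol article, Objectives) is: "To quantify the difference of prevalence in 1st-, 2nd-, 3rd- and 4th-degree perineal tears between the control and the TPUS-guided intervention arms". The section on data collections lists "incidence of any degree perineal tears" among the delivery outcomes taken from the medical record, so the graded data will exist.

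The statistical analysis plan section then defines the outcome for logistic regression as "perineal tears (≥ 3rd degree vs. none/1st–2nd degree"), using the same baseline covariates as the primary model. It sets two populations. The first is stated as "Third- and fourth-degree perineal tears will be analysed among all women reaching the second stage, with caesarean deliveries counted as no injury"; the second is women delivering vaginally. Odds ratios are to be "accompanied by absolute risks and risk differences by arm to facilitate clinical interpretation". For sparse outcomes: "For endpoints with a low expected number of events, Firth's penalised-likelihood estimation will be used". All secondary analyses are labelled exploratory, and "The trial is powered exclusively on the primary endpoint".

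No analysis by degree, of any tear, of 2nd degree or worse, or on the ordered scale is stated.

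**The concern.** The objective and the analysis do not ask the same question. The objective concerns the prevalence of each of four degrees. The analysis merges none, 1st and 2nd degree into one reference category and merges 3rd with 4th. Two of the four degrees named therefore have no estimate or interval by arm, and the other two have none separately. The promised absolute risks and risk differences belong to the same binary endpoint, so they do not fill the gap.

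At stake is whether the trial can describe an effect on perineal trauma where most tears are likely to lie. If training moved women from 2nd-degree to 1st-degree tears or to an intact perineum, the planned model would not register it. If the by-degree comparison is added only after the data are seen, the choice of cut-point will be open to question.

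**Working it through.** **1. Objective against analysis.**

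| Degree | Named in objective | Collected | Place in stated analysis |
|---|---|---|---|
| none | implied | yes | reference |
| 1st | yes | yes | reference |
| 2nd | yes | yes | reference |
| 3rd | yes | yes | event, merged with 4th |
| 4th | yes | yes | event, merged with 3rd |

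This step needs no assumption. Following the text as written gives no arm comparison for 1st- or 2nd-degree tears.

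**2. The plan's own figure.** The article gives no rate, event count or power for tears. Its one computed figure is the primary sample size: n per arm = 2 × (1.96 + 0.842)² × 53.5² / 20² ≈ 112.3, or 113.3 with the t distribution, rounded up to the stated 114. It reproduces and is not affected by this point.

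**3. How many severe tears.** Inputs:
- 114 women per arm (Sample size section). I also used 108, close to 134 × (1 − 0.19) = 108.5, the enrolled number less the hospital's 19% primary caesarean rate. That is a rough guide to vaginal births.
- Control rate of 3rd/4th-degree tears: not given, assumed 1% to 6%.
- Effect: assumed common odds ratio of 0.5.

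Treated rate = 0.5·o / (1 + 0.5·o), where o = p/(1 − p). At p = 3%, o = 0.0309 and the treated rate is 1.52%. Expected events = 114 × (0.03 + 0.0152) = 5.2.

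**4. Power, severe contrast against ordered scale.** None/1st/2nd are assumed in the ratio 27/30/40, with the severe rate on top. Fisher and Firth power come from enumerating the two binomial distributions; Firth is an unadjusted penalised likelihood-ratio test. Ordinal power uses Whitehead's formula: V = (N/12)(1 − Σp̄³), power = Φ(|ln OR|·√V − 1.96). At 3%: Σp̄³ = 0.105, V = 19 × 0.895 = 17.0, and 0.693 × 4.12 − 1.96 = 0.90, which gives 82%.

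Results at 114 per arm, odds ratio 0.5:

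| Control rate | Treated rate | Events, both arms | Fisher | Firth | Ordinal |
|---|---|---|---|---|---|
| 1% | 0.50% | 1.7 | <1% | <1% | 81% |
| 3% | 1.52% | 5.2 | 3% | 7% | 82% |
| 5% | 2.56% | 8.6 | 8% | 13% | 82% |
| 6% | 3.09% | 10.4 | 11% | 16% | 82% |

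At 108 per arm: 1.6 to 9.8 events, Fisher under 1% to 10%, Firth under 1% to 15%, ordinal 79% to 80%. Simulated Wilcoxon tests agree with the ordinal figures to within about 2 points.

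**5. Sensitivity.** At an odds ratio of 0.6 and 114 per arm, ordinal power is 56%, Fisher at most 7% and Firth at most about 12%. With a different assumed split (none 20%, 1st 35%, the rest 2nd degree apart from a severe rate of 1% to 5%), ordinal power is 81% to 82% for a twofold odds ratio and 38% to 39% for 1.5.

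**6. Model size.** The covariates are "maternal age, body mass index at enrolment, gestational age at randomisation, maternal height, and sonographic estimated fetal weight". With the arm, that is 6 parameters. At 1.7 to 10.4 events there are 0.3 to 1.7 events per parameter.

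**The case against.** A reader might infer that the tear objective gets no usable answer at all. The article does not support that. Severe tears receive an adjusted odds ratio with a 95% CI, absolute risks and a risk difference, in two populations, with an estimator suited to sparse data. Severe tears are also a defensible clinical contrast, since the article's own rationale stresses severe perineal tears and pelvic-floor injury.

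A reader might also infer that low power here is an error, or that a real benefit would be reported as no difference. Neither follows. The trial claims power only for the primary endpoint, and secondary results are to be read as estimates with intervals; a wide interval is not a finding of no difference. Planning Firth estimation is sound handling, not an admission of a flaw.

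The figures have limits too. Every tear rate is assumed. Fisher's test is not the planned analysis and understates its power about twofold at a 3% rate, which is why the Firth column is shown. The ordinal power holds only if one odds ratio applies at every cut-point, which nothing in the article establishes.

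Finally, a table of tears by degree could sit in a fuller document that is not shown. But the article does not leave tears open: it fixes the endpoint, model, covariates, sparse-data method and populations, and what it fixes does not match its objective. These objections lower the severity but leave the mismatch standing.

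**Conclusion.** The point holds as a mismatch between a stated objective and a stated analysis. First- and second-degree tears have no planned between-arm estimate, and movement among none, 1st and 2nd degree is invisible. That conclusion rests on the text alone.

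The size is conditional. With an assumed severe-tear rate of 1% to 6%, 108 to 114 women per arm and a common odds ratio of 0.5, about 2 to 10 severe tears are expected in total. Power on the planned contrast stays at or below about 16%, against roughly 80% on the ordered scale. The ranking is stable across the assumed rates but depends on proportional odds: if benefit were confined to severe tears, the ordinal model would lose its advantage. Severity is minor to moderate; the primary endpoint and sample size are untouched.

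**What to change.** In the statistical analysis plan section:

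- Report counts for each tear degree (none, 1st, 2nd, 3rd, 4th) by arm, with risk differences and 95% CIs. This alone answers the objective as worded.
- Add one exploratory proportional-odds model of tear degree (0 = intact to 4) with the same baseline covariates and in the same two populations, caesarean counted as 0 in the first. Give the common odds ratio with 95% CI, and show the odds ratio at each cut-point as a check on the common-odds assumption.
- Keep the 3rd/4th-degree Firth analysis as the separate clinical contrast.

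The cost is one table and one extra exploratory model, on data already collected. The downside is the model's reliance on proportional odds, which the cut-point odds ratios expose, though imprecisely at the severe end. If the investigators want severe tears only, the alternative is to narrow the objective to 3rd/4th degree; that restores consistency but gives up the comparison of the milder degrees. Either change should be made before the data are analysed.

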### Sample size

The sample size was calculated to detect a mean reduction of 20 minutes in the duration of the active second stage of labour in the experimental group compared with the control group. Twenty minutes was pre-specified as the minimal clinically important difference for the duration of the active pushing phase, rather than as the anticipated magnitude of the treatment effect. Its clinical relevance is anchored to preliminary data showing that nulliparous women with LAM co-activation experience a longer second stage than those without co-activation (83 ± 63 vs. 63 ± 42 minutes, respectively). The pooled standard deviation is 53.5 minutes, yielding a standardised effect size (Cohen’s d) of 0.37, corresponding to a small-to-medium effect consistent with published trials of intrapartum ultrasound-based biofeedback interventions which were delivered intrapartum rather than antenatally. Using a two-sided independent-samples test with α = 0.05 and 80% power, the required sample size is 114 participants per arm (228 total). To account for an anticipated 15% attrition rate, encompassing study dropout, caesarean delivery before or during labour, and operative vaginal delivery precluding assessment of the primary endpoint, the final enrolment target has been set at 268 participants (134 per arm). We acknowledge that the hypothesised effect size assumes a biologically plausible benefit across the entire intervention group. Because preliminary data suggest that approximately 25% of nulliparous women exhibit LAM co-activation, the treatment effect may be attenuated in the overall population if benefit is concentrated in this subgroup. A pre-specified within-arm analysis by co-activation status at training is planned to explore this hypothesis (see Statistical Analysis Plan).

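### The exploratory within-arm comparison by co-activation status has no stated protection against unequal variances, although the plan's own preliminary SDs (63 and 42 minutes) point to them

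*Protocol article*

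**What the plan says.** The Sample size section explains that benefit may be concentrated in women with levator ani co-activation, and announces a within-arm analysis by co-activation status at training to explore this. The Statistical analysis plan section lists it among the subgroup analyses as "Within-arm analysis of levator ani function (intervention arm only"). It says that subgroup effects will come from interaction terms in the regression models, with stratum-specific 95% intervals. The regression for pushing time is multivariable linear regression. No variance estimator is named for it.

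One clause protects the intervals of that model: "If the residuals of the linear model indicate substantial departure from normality, a bootstrap confidence interval will be computed". It stands in the paragraph on the primary endpoint.

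The Sample size section also gives the preliminary data for the two groups: women with co-activation have a "longer second stage than those without co-activation (83 ± 63 vs. 63 ± 42 minutes, respectively"). The Statistical analysis plan section says the assumed SD was derived from the active pushing phase, so these SDs describe the primary endpoint. On group sizes, the Sample size section says that "approximately 25% of nulliparous women exhibit LAM co-activation"; the Abstract and Introduction give 15–20%.

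**The concern.** A linear model fitted with default standard errors assumes one residual variance. The preliminary figures contradict that for exactly this grouping: the variance ratio is 63²/42² = 2.25. The direction is the harmful one. When the smaller group has the larger variance, the pooled estimate is dominated by the larger, less variable group, and the standard error of the difference comes out too small.

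The stated fallback checks a different assumption. It reacts to non-normal residuals, not to unequal spread, and it is not restated for the subgroup models, although a bootstrap is restated for blood loss.

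Secondary and subgroup results are to be reported as estimates with 95% intervals and no multiplicity correction, so the interval is the reader's main guide to uncertainty. If it is too narrow, a chance difference between co-activators and other women will look firmer than it is.

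**Working it through.** **The plan's own figure.** Pooled SD = √[(63² + 42²)/2] = 53.5 and d = 20/53.54 = 0.37, as stated ("The pooled standard deviation is 53.5 minutes, yielding a standardised effect size (Cohen’s d) of 0.37"). With a 20-minute difference and SD 53.5, a t-based calculation gives 113.3, hence 114 per arm, which agrees with "Using a two-sided independent-samples test with α = 0.05 and 80% power, the required sample size is 114 participants per arm (228 total"). The plan gives no precision figure for the within-arm analysis.

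**Inputs.** SDs of 63 and 42, and prevalence 15%, 20% or 25%, come from the document. The number of women in the intervention arm is 114 (analysed) or 134 ("the final enrolment target has been set at 268 participants (134 per arm")). Two things are assumed: the outcome is pushing time, and the preliminary SDs hold in trained women.

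**Formulas.**
- True SE = √(63²/n₁ + 42²/n₂)
- Equal-variance SE = √{[((n₁−1)·63² + (n₂−1)·42²)/(N−2)]·(1/n₁ + 1/n₂)}
- Coverage = 2Φ(t·ratio) − 1, where ratio = equal-variance SE / true SE and t is the 97.5% point on N−2 degrees of freedom

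**Worked case, 25% of 114 (28 vs 86).**
- True SE = √(3969/28 + 1764/86) = √(141.75 + 20.51) = 12.74 minutes.
- Pooled variance = (27·3969 + 85·1764)/112 = 2295.6. Equal-variance SE = √[2295.6·(1/28 + 1/86)] = 10.42 minutes.
- Ratio 0.818; coverage 89.5%.

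| Prevalence | n₁ vs n₂ | Equal-variance SE | True SE | True / equal-variance | Coverage | False-positive rate |
|---|---|---|---|---|---|---|
| 15% | 17 vs 97 | 11.99 | 15.86 | 1.32 | 86.6% | 13.4% |
| 20% | 23 vs 91 | 10.94 | 13.85 | 1.27 | 88.2% | 11.8% |
| 25% | 28 vs 86 | 10.42 | 12.74 | 1.22 | 89.5% | 10.5% |

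With all 134 women the coverages are 86.5%, 88.2% and 89.7%. More women do not help, because the error depends on the group proportions.

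**Simulation with the document's means and SDs** (N = 114, no covariates; 20,000 replicates, but 1,000 for the bootstrap and the residual test):

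| Durations | Prevalence | Equal-variance | Welch | Bootstrap resampling women | Shapiro test rejects |
|---|---|---|---|---|---|
| Normal | 15% | 86.5% | 95.1% | 93.4% | 11% |
| Normal | 20% | 87.9% | 95.0% | 94.1% | 12% |
| Normal | 25% | 88.9% | 94.6% | 91.8% | 13% |
| Gamma | 15% | 86.1% | 93.0% | 90.7% | 99% |
| Gamma | 20% | 87.5% | 93.2% | 93.1% | 99% |
| Gamma | 25% | 89.3% | 93.9% | 92.9% | 100% |

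The bootstrap figures carry a Monte Carlo standard error of about √(0.93·0.07/1000) = 0.8 points, so I quote them as about 91–95%. A separate simulation of the regression with five covariates gave 86–89% for ordinary standard errors and 93–95% for HC3. The Shapiro test stands in for the plan's check of residuals, for which the article gives no threshold.

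**Why the primary contrast escapes.** With n per arm, the pooled SE² is [(s₁² + s₂²)/2]·(2/n) = (s₁² + s₂²)/n, which equals the unequal-variance SE². With 1:1 allocation and near-equal numbers analysed, unequal SDs do no harm there.

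**The case against.** The strongest reply is that the document never says that equal-variance standard errors will be used. It says linear regression, and an article may leave the standard-error option for an exploratory subgroup to a fuller plan. That stands. A reader might infer that the plan prescribes a common residual SD and that its intervals therefore will cover only 86–90%. The text supports only the weaker statement that this follows if the usual software default is taken.

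Second, if the primary model is carried over to this subgroup, its bootstrap clause may fairly be carried over too. Durations of 83 ± 63 minutes can hardly be normal, and the simulated check rejected in 99–100% of gamma samples. Resampling women would then recover much of the loss, leaving Welch ahead by only 0.1 to 2.8 points in the runs above. This also stands, with limits. The clause is written for the primary model. Its trigger fired in only 11–13% of samples when durations were normal with unequal SDs. The type of bootstrap is not stated, and resampling residuals across groups would reimpose a common variance.

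Third, the SDs are preliminary, and training aimed at co-activation may change them. If they became equal, coverage would be nominal. The outcome of this subgroup analysis is also not named in the list; pushing time is inferred from the Sample size section.

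Finally, all subgroup analyses are declared exploratory, and no trial decision rests on this one.

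**Conclusion.** The point holds as a conditional and minor one. With equal-variance standard errors, SDs of 63 and 42 in the trained arm and 15–25% co-activators, nominal 95% intervals cover about 86–90%, and the false-positive rate is roughly 10–13% instead of 5%. If the bootstrap is carried over with women as the resampling unit, coverage is about 91–95%.

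Three wider readings are not supported. The primary treatment contrast is not affected, because the arms are equal in size. The same criticism cannot be given a size for the epidural or fetal-malposition analyses, because the document reports no SDs for those groups. Nor would a better interval turn this into a test of effect modification: with the intervention arm alone there is no arm-by-co-activation interaction to estimate, so the result remains a within-arm association.

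**What to change.** Add one sentence to the subgroup paragraph of the Statistical analysis plan section: the within-arm comparison of pushing time by co-activation status uses HC3 or Welch-type 95% intervals, whatever the residual normality check shows.

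The cost is that sentence and one option in R or Stata. Under the preliminary SDs the interval becomes about 22% wider than the equal-variance one at 25% prevalence (12.74/10.42) and about 32% wider at 15% (15.86/11.99). Sample size, recruitment, data collection and the primary analysis do not change.

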**Methods and analysis:**

PURSUE is a single-centre, open-label, parallel-group RCT at Fondazione Policlinico A. Gemelli, Rome reported according to the SPIRIT 2013 and CONSORT 2010 guidelines. Nulliparous women between 28 + 0 and 37 + 0 weeks of gestation will be randomised 1:1 to midwife-led pushing training without ultrasound biofeedback or a midwife-led session combining theoretical instruction with real-time TPUS-guided pushing training. The primary endpoint is duration of the active second-stage of labour (minutes). Secondary outcomes include levator ani co-activation amplitude, spontaneous vaginal birth, perineal trauma, postpartum haemorrhage ≥ 500 mL, urinary/faecal incontinence at 6, 12 and 16 weeks postpartum and childbirth experience (CEQ-2). A sample of 228 (114 per arm) provides 80% power to detect a clinically meaningful reduction of 20 minutes(Cohen’s d = 0.37; α = 0.05, two sided). Allowing for 15% attrition, 268 women will be enrolled. The primary analyses uses multivariate linear regression adjusting for pre-specified covariates; secondary analyses are exploratory.

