### Study procedures

Study procedures are summarized in Fig 2. Pregnant women between 28 + 0 and 37 + 0 weeks of gestation who participate in the antenatal preparation course sponsored by the Fondazione Policlinico Agostino Gemelli IRCCS will be informed about this study. The antenatal preparation course is held monthly, and it encompass nearly 60 women per course. Women who express interest will be scheduled for an in-person appointment with a research midwife, during which they will undergo eligibility screening. Those meeting the inclusion criteria and providing written informed consent will be randomized into one of two groups:

Midwife-led TPUS-guided pushing training group.Midwife-led pushing training only group (control).

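### Splitting gestational age at 35 weeks wastes information if the training effect changes steadily with timing; a continuous interaction costs almost nothing

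*Protocol article*

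**What the plan says.** Under the heading on the statistical analysis plan, the second of three pre-specified subgroup analyses is "gestational age at intervention (28–34 weeks vs. 35–37 weeks". The method is stated: "Subgroup effects will be estimated via interaction terms in the regression models and reported as stratum-specific effect estimates with 95% CIs". The article says that this subgroup and the epidural subgroup "are defined by post-randomisation variables and are reported as exploratory only". It also regards all subgroup analyses as hypothesis-generating and says the trial is powered only on the primary endpoint.

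The primary model adjusts for baseline covariates that include "maternal age, body mass index at enrolment, gestational age at randomisation, maternal height". The form in which gestational age enters that model is not stated, and the covariate is the value at randomisation, whereas the subgroup uses the value at intervention.

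The window comes from the abstract, "Nulliparous women between 28 + 0 and 37 + 0 weeks of gestation will be randomised 1:1", and from Study procedures, where the women informed about the study are "Pregnant women between 28 + 0 and 37 + 0 weeks of gestation". Neither passage caps the date of the training session itself.

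**The concern.** Gestational age is a continuous quantity. With two bands, a woman trained at 28+0 counts the same as one trained at 34+6, while 34+6 and 35+0 count as different. If training nearer to birth works better or worse by degrees, a two-level indicator follows that pattern poorly. The narrow late band also leaves its own estimate imprecise. How the effect depends on timing is a practical question for a monthly antenatal course that enrols over nine weeks of pregnancy, and the stratum estimates are what readers will see. At stake is how well an exploratory question is answered, not the primary comparison.

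**Working it through.** **The plan's own figure.** The article gives no figure for this subgroup, so the inputs come from its sample size section. The pooled SD is √((63² + 42²)/2) = 53.5 minutes. For 20 minutes, two-sided α of 0.05 and 80% power, the normal formula 2 × (1.96 + 0.84)² × 53.5²/20² gives 113 per arm and the t-test gives 114, as stated. I use N = 228, 1:1 allocation and SD 53.5.

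**Assumption.** The distribution of gestational age is not given. The base case is even enrolment by day over 28+0 to 37+0, which is 64 days: 49 in the early band (28+0 to 34+6) and 15 in the late band (35+0 to 37+0).

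**Band sizes.** Late share p = 15/64 = 23.4%, or about 53 of 228 women. The early band has about 175.

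**Information kept.** If the effect is linear in gestational age, the two-band interaction keeps a share equal to the squared correlation between the band indicator and gestational age:

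- variance of gestational age = (64² − 1)/12 = 341.25 days², so SD = 18.5 days = 2.64 weeks
- difference between band means = 32 days
- share kept = p(1 − p) × 32²/341.25 = 0.234 × 0.766 × 1024/341.25 = 0.54, a loss of 46%

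Treating the window as continuous (2 of 9 weeks in the late band) gives a 48% loss.

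**Precision by band.** The half-width is 1.96 × 53.5 × √(4/n):

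- late: 1.96 × 53.5 × √(4/53.4) = ±28.7 minutes
- early: 1.96 × 53.5 × √(4/174.6) = ±15.9 minutes

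**Sensitivity to the assumption.**

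| Assumed enrolment | Late share | Loss | Late-band half-width |
|---|---|---|---|
| Even, 28+0 to 37+0 | 23% | 46% | ±29 min |
| Even, to 37+6 | 30% | 37% | ±25 min |
| Bell-shaped, centred at 35 weeks, SD 2 | 41% | 39% | ±22 min |
| Falling linearly with gestational age | 5% | 75% | ±62 min |
| Bell-shaped, centred at 31 weeks, SD 2 | 2% | 85% | ±92 min |

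**Power for a gradient.** Take a benefit that rises from 0 minutes at 28 weeks to 40 minutes at 37 weeks, so 20 minutes at mid-window: 40/9 = 4.44 minutes per week.

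- Continuous term: SE = (2 × 53.5/√228)/2.64 = 2.69 minutes per week; z = 4.44/2.69 = 1.65; power Φ(1.65 − 1.96) = about 38%.
- Two bands: z = 1.65 × √0.54 = 1.21; power Φ(1.21 − 1.96) = about 23%.

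**Model-based effect late in the window.** At 36 weeks, 3.5 weeks above the mean, the linear model's half-width is 1.96 × √(7.09² + 3.5² × 2.69²) = about ±23 minutes, where 7.09 = 2 × 53.5/√228. This is narrower than the band estimate but still above 20 minutes.

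**The case against.** The strongest reply is that the plan already limits this analysis. It is labelled exploratory, it comes with confidence intervals that will show how wide the late band is, and no confirmatory claim hangs on it. Two pre-specified bands are a common and readable display. That stands, and it is why the point is small.

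It is also fair to say that the advantage of a continuous term depends on a gradient, which the article does not hypothesise. The squared correlation is symmetric: if the truth were a step at 35 weeks, the linear term would keep the same 54% in the base case. A reader might infer that the continuous form wins whatever the truth, or loses only slightly under a step. The arithmetic does not support that.

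Nor is the cut the main limit on power. At 38% against 23% for a substantial gradient, neither form is adequate.

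A reader might also infer that gestational age already sits in the primary model as a continuous covariate. The article does not say so, and it names gestational age at a different time from the one that defines the subgroup. Any fix has to say which variable it uses.

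What the reply does not do is justify setting aside information already collected. Exploratory status limits what may be claimed; it gives no reason to prefer the less informative summary of a possible gradient.

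**Conclusion.** The point holds as a cheap improvement. Given a steady change of effect with gestational age, the two-band test loses about 46% of the information under even enrolment over 28+0 to 37+0, about 37% if the late band extends to 37+6, and 39% to 85% under the other shapes tabulated. These losses rest on a linear gradient and on assumed enrolment patterns. No single figure can be put to the plan as fact.

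It would go too far to say that the late band has almost no precision. In the base case it holds about 53 women, and its interval is about 1.8 times as wide as the early band's. It is too imprecise to judge a 20-minute difference. It would come close to uninformative only if few women fall at 35 to 37 weeks, which the article neither states nor rules out. It would also go too far to say that most of a real gradient is lost, since the base case keeps 54%. The primary analysis is not touched.

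**What to change.** In the subgroup paragraph of the statistical analysis plan, define the effect-modification analysis as an arm × gestational age interaction in continuous weeks, using gestational age at randomisation. That is a baseline value already listed among the primary-model covariates, so it also avoids a post-randomisation modifier. Report the change in treatment effect per week with its 95% CI, and model-based effects at several gestational ages, for example 30, 33 and 36 weeks. Keep the 28–34 and 35–37 week estimates as a descriptive display, and state whether the late band ends at 37+0 or 37+6.

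The cost is a sentence or two and no new data. There are two downsides. The linear term assumes a gradient and would lose a similar share of information under a true step at 35 weeks, which is why the band estimates stay. And gestational age at randomisation stands in for gestational age at training, which matters only if the gap between the two is long or varies much between women. The analysis should keep its exploratory label.
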